#### Individual analyses

At the individual level, we will examine the hypothesized pathways using structural equation models while controlling for dependency due to school attended as noted above. Across Genesee County, there are an average of 180 4th–6th Graders in Flint schools resulting in a maximum sample size of 3600 students over the course of the study (we use a 33% consent/retention rate for calculations). Using the SEM power calculations suggested by MacCallum, Browne, and Sugawara (1996), we will have ample statistical power in SEM analyses for even our most complex models with 100 degrees of freedom (*df*). Power is based on the probability of rejecting the hypothesis of not a close fit with the data when the true model fit is excellent (the most stringent test). Our power with the 1200 (600 per condition) students is over .80. Notably, MacCallum et al. (1996)^.^ show that power of .80 is achievable with alpha = .05 and *df* of 100 with a sample as small as 178 for test of not-close fit.

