### Sample

#### Schools

We will recruit 20 schools and implement the intervention across three school years (see Table 1). Co-educational elementary schools in Genesee County Intermediate School District (GISD), Michigan will be invited to participate. Schools participating will be similar in terms of proportion of students receiving free/reduced school lunches and approximate size of the school. Prior to the intervention roll-out, all 20 schools will be randomized to intervention or control. The intervention will be implemented in stages. Cohort 1 schools will include 5 intervention and 5 control schools. Cohort 2 will include10 additional schools (5 intervention and 5 control) for a total of 10 intervention and 10 control schools; each school will implement the intervention for two years.

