#### Student eligibility and recruitment

There are 21 public school districts and 13 academies (charter schools) serving over 67,000 students in the GISD. Recruitment efforts will begin with presentations to the superintendents of the schools and academies. This will be followed up by similar presentations and briefings to school building principals and/or their designees (dean of students, academic services, teachers). The briefings explain the goals of the research project, the benefits to participating schools, anticipated intervention and research activities, eligibility, and similar issues. Eligibility includes having at least two grades between grades 4–6 and having a student population with 50% or higher free or reduced school lunch eligibility, being involved in MIBLISI (Michigan’s Integrated Behavior and Learning Support Initiative) and PBIS (Positive Behavioral Interventions & Supports) and being committed to the project. Across Genesee County, there are currently an average of 180 4th–6th graders in each school resulting in a maximum sample size of 3600 students over the course of the study (using a 66% consent/retention rate).

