### Power analyses

#### Between group analyses

Since the proposed intervention will be delivered within group (school) settings, data analyses examining treatment effects at the school level must account for the correlation among observations within school (i.e., intraclass correlations; ICC) due to shared factors within a school setting such as school selection factors (e.g., school attendance boundaries, family choice), similarities in treatment experiences (e.g., staff factors, resource factors), and within-school influences (e.g., common experiences with other students, cultural norms). Previous analyses of measures to be used in this study indicate small ICCs within schools for our outcome variables of interest (range: .00 to .03). If an ICC greater than zero is ignored, the outcome variance due to between-school differences (which can be large) is mixed with outcome variance due to between-participants variability within schools (which can be small because of the correlation). This can lead to large standard deviations, larger *p* values, and false-negative results (Chuang, Hripcsak, & Heitjan, 2002; Murray, Phillips, Bimbaum, & Lytle, 2001). Thus, our analytic strategy described below takes the ICC into account. Assuming 20 schools, 60 students per school, and a modest within-cluster correlation coefficient (ρ = .10), we will be able to detect standardized effect sizes at the school level of *d* = .27, representing a medium effect size, with probability (β > .80). Thus, our design will include 20 schools over the course of 2 years of the study period. The lagged implementation, however, limits across school comparisons (i.e., treatment vs control schools) until year three.

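### The 3,600 maximum carries two different consent/retention rates, and the individual-level power figure covers overall model fit, not the intervention pathways it is offered for

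*Protocol article*

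**What the plan says.** The protocol article describes the student sample twice. Student eligibility and recruitment starts from an average of 180 students in grades 4 to 6 per school, "resulting in a maximum sample size of 3600 students over the course of the study (using a 66% consent/retention rate"). Individual analyses, under Power analyses, starts from the same 180, "resulting in a maximum sample size of 3600 students over the course of the study (we use a 33% consent/retention rate for calculations").

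The school count is fixed in the Schools section: "for a total of 10 intervention and 10 control schools". The between-group power calculation rests on "Assuming 20 schools, 60 students per school, and a modest within-cluster correlation coefficient (ρ = .10"), while the same section says that earlier analyses "indicate small ICCs within schools for our outcome variables of interest (range: .00 to .03").

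Individual analyses sets out to examine the hypothesised pathways by structural equation modelling, with control for school attended. It then states that "we will have ample statistical power in SEM analyses for even our most complex models", with 100 degrees of freedom, and that "Our power with the 1200 (600 per condition) students is over .80". It makes clear that this is the probability of rejecting a not-close fit when the true fit is excellent, and cites 178 as the smallest sample that gives power .80 at alpha .05.

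**The concern.** There are two linked faults.

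**Sample base.** One maximum cannot come from both 66% and 33%, and here it comes from neither. A reader cannot tell how many students the trial expects to analyse.

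**Power claim.** The hypothesis in the Analysis section is a chain: the intervention improves perceived climate, and climate in turn improves mental health. A global fit test asks whether the model as a whole reproduces the observed covariances. A model can fit closely while its intervention path is zero, so high power for fit does not imply power for the path. The intervention varies only between schools, so the first link has the precision of a comparison of 10 schools with 10. The article gives no power for that link, yet calls power ample in the paragraph that introduces the pathways.

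At stake is how a null mediation result would be read. A reader relying on the word ample could take it as evidence against the climate mechanism when power for the path was never established.

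**Working it through.** **1. Sample base.** Inputs: 180 students per school (both sections) and 20 schools.

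- 180 x 20 = 3,600, so the maximum is full enrolment before any rate.
- At 66%: 3,600 x .66 = 2,376, or 2,376 / 20 = 118.8 per school.
- At 33%: 3,600 x .33 = 1,188, or 1,188 / 20 = 59.4 per school.
- If 3,600 were what remained after 66%, the base would be 3,600 / .66 = 5,455, which 20 schools of 180 cannot supply.
- The power sections use 60 per school and 20 x 60 = 1,200. Only 33% matches.

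**2. The article's own fit-test figure.** Inputs from Individual analyses: df = 100, alpha = .05, N = 1,200, cited minimum 178. The article does not give RMSEA values. I assume .05 under the null and .01 under the alternative, because these return the cited minimum.

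The noncentrality is (N - 1) x df x RMSEA². Power is the probability, under the alternative, of falling below the 5% point of the null noncentral chi-square.

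- N = 177: power .799. N = 178: power .802. The cited minimum reproduces.
- N = 1,200: power about 1.00. The claim of more than .80 is correct for overall fit with independent observations.

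No effect size for any path, ICC or design effect enters this calculation.

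**3. Power for the intervention-to-climate path.** The article gives no figure to reproduce. Inputs: 20 schools, 60 students each, and the ICCs in Between group analyses (.00 to .03 reported, .10 for planning). I borrow d = .27 from that section as an illustration only; there it is a detectable effect, not an expected effect on climate. The calculation uses one unadjusted post-test and total SD 1.

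DE = 1 + (60 - 1) x ICC; SE = √(4 x DE / 1,200); noncentrality = .27 / SE. Power is from the noncentral t with 20 - 2 = 18 df, two-sided alpha .05 (critical value 2.101).

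| ICC | DE | SE | Noncentrality | Power |
|---|---|---|---|---|
| 0 | 1.00 | .0577 | 4.68 | 99% |
| .01 | 1.59 | .0728 | 3.71 | 94% |
| .02 | 2.18 | .0852 | 3.17 | 85% |
| .03 | 2.77 | .0961 | 2.81 | 76% |
| .10 | 6.90 | .1517 | 1.78 | 39% |

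Where the indirect effect is declared only if both of its links are significant, the power of this first link is an upper limit.

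**4. Sensitivity.** At 66% (118.8 per school), power is 83% at ICC .03 and 41% at ICC .10. At 60 per school, if baseline adjustment removed 25% of the variance (an assumption), power at ICC .03 would be 87%.

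**The case against.** The best defence is that no stated power figure is wrong. The article says plainly that its power refers to fit, its minimum of 178 reproduces, and 1,200 is far above it. It marks 33% as the rate for calculations and uses that lower rate consistently, so the conflict with 66% cannot have inflated the power. A condensed article may also leave path power to a fuller plan. All of this stands except the last step: having chosen to claim ample power in the paragraph on pathways, the article needs a figure that bears on them.

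Three stronger readings are tempting, and the documents do not support them.

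- A reader might infer that clustering defeats the fit test, because 1,200 / 6.9 = 174 is below 178. Dividing N by a design effect for a cluster mean is only a rough device for a covariance-structure test. Even if accepted, it moves power only to .79 at ICC .10 and leaves it above .99 at ICC .03.
- A reader might infer that the analysis ignores clustering. The article says that dependency due to school is controlled; the gap is in the power figure only.
- A reader might infer that the mediation analysis is underpowered, at 39% to 76%. Those are the two least favourable rows of the table. Over most of the article's reported ICC range, power at d = .27 is higher. The rows also ignore the Fall Year 1 climate measurement listed in Table 2, which could be used for adjustment.

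**Conclusion.** The point holds in two parts.

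The sample statement is wrong as written. 3,600 is full enrolment, the two rates attached to it imply analysed samples that differ twofold (1,188 against 2,376), and only 33% is compatible with the power calculations. This part is simple arithmetic on the article's own numbers.

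The word ample is unsupported for the pathways. The fit-test power is correct but answers a different question. Whether power for the intervention path is adequate depends on the ICC for climate and on the effect assumed. In the illustration it is at or above 85% for ICCs up to .02, slightly short of 80% at .03, and poor at the planning value of .10. These figures rest on d = .27, 60 per school, equal cluster sizes, 18 df and no baseline adjustment; adjustment would raise them. They show that the claim is unproven, not that the analysis must fail. Mechanisms are a secondary aim, so this should be corrected but does not threaten the primary comparison.

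**What to change.** 1. In both Student eligibility and recruitment and Individual analyses, state about 3,600 enrolled, one reconciled consent/retention rate, and the analysed number that follows: about 1,190 (59 per school) at 33%, or about 2,380 (119 per school) at 66%. If 66% is kept, the 60 per school and the 1,200 in the power sections must be updated too.
2. Limit the statement of power over .80 to overall model fit.
3. Replace the claim of ample power for the pathways with the power of the intervention-to-climate path across the article's own ICCs. At 60 per school the row would be, for an illustrative d = .27: 99%, 94%, 85% and 76% at ICC 0, .01, .02 and .03, and 39% at .10. Give the assumptions, and note that baseline adjustment would raise these values. Recompute them if the rate in step 1 changes the number per school.

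The cost is rewording and one short calculation. No new data and no change of design are needed, though the stated power becomes less favourable at the higher ICCs.

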### Analysis

Our primary hypothesis is that students in schools receiving the intervention will report less violence (over time) compared to students in the control group. We also hypothesize that the intervention schools have an overall lower rate of violence over the school year compared with control schools. We expect that using implementation facilitation led by a climate specialist as part of a 3-person leadership team is a feasible and sustainable approach to integrating and effectively delivering the three intervention components. Finally, we expect that students in the intervention schools will report more positive school climate compared with those in control schools and that this, in turn, will result in lower improved mental health outcomes.

A cluster randomization design is proposed with random assignment by school to one of two arms: intervention or control. Evaluation of effectiveness outcomes will involve testing at four time points: a fall of Year 1, spring of Year 1, fall of Year 2, spring of Year 2. Measures will include school records and self-report data from students and teachers. The survey of students makes use of currently collected MiPHY data. Ten schools will be recruited in the first year and 10 in the following year; staggered recruitment will allow some initial evaluation testing of the program and allow the earliest possible start time with a number of schools. Including 20 schools in the research provides an opportunity to examine school level differences. To adjust for bias introduced by multiple comparisons across our outcome variables, we will use a pair of conservative (Tukey and Bonferonni) *p*-value adjustments in addition to reporting direct effect sizes (e.g., group differences in means) to allow for assessment not dependent on standard null hypothesis testing.

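### The SEM power statement treats 100 df as the demanding case, but power of the not-close-fit test rises with df, so it does not carry over to smaller models

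*Protocol article*

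**What the plan says.** The Individual analyses section, under Power analyses, plans structural equation models for the hypothesized pathways, controlling for dependency due to school. It takes 3,600 students as the maximum and notes "we use a 33% consent/retention rate for calculations", which gives about 1,200.

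The power claim has four parts:

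- The general claim: "we will have ample statistical power in SEM analyses for even our most complex models with 100 degrees of freedom".
- The test: "Power is based on the probability of rejecting the hypothesis of not a close fit with the data when the true model fit is excellent".
- Stated result, with no df attached in that sentence: "Our power with the 1200 (600 per condition) students is over .80".
- The supporting benchmark, at 100 df: "power of .80 is achievable with alpha = .05" and "with a sample as small as 178 for test of not-close fit".

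No df other than 100 is given. The pathway itself is in the Analysis section, which expects that "students in the intervention schools will report more positive school climate compared with those in control schools and that this, in turn", will improve mental health.

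**The concern.** The word 'even' sets up an argument from the hardest case: if power is ample at 100 df, simpler models must be safe too. For the test of not-close fit this runs the wrong way. Each additional df adds information about overall fit, so among the models the sentence covers, 100 df is the easiest to power. Adequacy there says nothing about a model with few df.

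What is at stake is the basis of a printed power claim for the mechanisms aim. A reader would take power above .80 as established for any pathway model up to 100 df. The calculation shown establishes it at 100 df only.

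**Working it through.** **Inputs from the article.** Test of not-close fit; alpha .05; benchmark N = 178 at 100 df for power .80; N = 1,200 (3,600 × .33 = 1,188). For the clustering illustration, from Between group analyses: 60 students per school, ICCs of .00 to .03 from earlier analyses, and an assumed correlation of .10.

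**Assumed input.** The RMSEA values are not printed. I used .05 under the null and .01 as the true value, because this pair returns the printed benchmark.

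**Formulas.**

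- Noncentrality: λ = (N − 1) × df × RMSEA².
- Critical value c: the 5th percentile of the noncentral chi-square with df and λ at RMSEA .05.
- Power: the probability that a noncentral chi-square with df and λ at the true RMSEA falls below c.

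**Step 1: reproduce the plan's figure.** At N = 178 and df = 100, null λ = 177 × 100 × .0025 = 44.25 and true λ = 177 × 100 × .0001 = 1.77. Then c = 113.78 and power = .802. At N = 177 power is .799, so the minimum is 178, as printed. Other pairs do not return it: .05 against 0 gives 168; the close-fit test (.05 against .08) gives 132; the exact-fit test (0 against .05) gives 164.

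**Step 2: the plan's N at 100 df.** At N = 1,200 power is about 1.00, so the statement that it exceeds .80 is correct there.

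**Step 3: same N, fewer df.** For example, at 1 df null λ = 1,199 × 1 × .0025 = 2.9975, true λ = 0.1199, c = 0.0749 and power = .20.

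| df | Power, true RMSEA .01 | Power, true RMSEA 0 |
|---|---|---|
| 1 | .20 | .22 |
| 2 | .43 | .47 |
| 3 | .59 | .64 |
| 4 | .71 | .76 |
| 5 | .79 | .85 |
| 6 | .86 | .90 |
| 10 | .97 | .99 |
| 100 | about 1.00 | about 1.00 |

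The N needed for power .80 (true RMSEA .01) falls in the same direction: 4,039 at 1 df, 2,382 at 2, 1,216 at 5, 750 at 10, 474 at 20, 268 at 50 and 178 at 100.

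**Step 4: clustering, as an illustration.** I used the simple design effect 1 + 59 × ICC, which is only an approximation for a fit test.

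- ICC .03: 1 + 59 × .03 = 2.77, so effective N = 1,200 / 2.77 ≈ 433. Power is .32 at 6 df, .47 at 10 and .75 at 20; about 23 df are needed for .80.
- Correlation .10: 1 + 59 × .10 = 6.9, so effective N ≈ 174. Power at 100 df is about .79.

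**The case against.** The strongest reply is that no printed figure is wrong. The benchmark of 178 reproduces exactly, power at 1,200 students and 100 df is about 1.00, and the sentence claiming power above .80 stands between two sentences about 100 df. That stands: the fault lies in the inference, not in the numbers.

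Second, no section describes a model with 1 to 5 df. Climate and mental health are measured at four time points, the Mechanisms section speaks of survey items, and records are linked across years, all of which suggests larger models. For illustration, a first-order cross-lagged model of climate and one outcome over four waves on scale scores has 36 − 24 = 12 df, and power .99 at N = 1,200. Small models cannot be ruled out, since composite variables are mentioned under Dichotomous outcome variates. A model of arm, climate and one outcome on scale scores has 1 df if the direct path is omitted. With that path it is saturated, and no fit test applies. So the low power values are conditional.

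Third, a reader might infer that a small, correctly specified model would fail the fit test and that the failure would count against the conceptual framework. The article does not support this. It uses the not-close-fit test for the power calculation and nowhere makes it the criterion for accepting the framework. Failure more often than not would also apply only at 1 and 2 df.

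None of this rescues the argument from 100 df to simpler models.

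**Conclusion.** The point holds as a fault of direction in the stated reasoning. Power for this test rises with df, so 100 df is a favourable case, and the claim of ample power is shown for that case alone.

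The size is conditional. If a planned pathway model has 1 to 5 df, power at 1,200 independent students is .20 to .79 (true RMSEA .01); with true RMSEA 0 it is below .80 at 1 to 4 df and .85 at 5. This rests on the inferred RMSEA pair, on independence between students, and on df that the article does not give. Clustering would lower the values.

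Two stronger readings are tempting. One is that the trial lacks power for its mediation analysis; the article does not give the df needed to say so. The other is that 6 df is the safe minimum. That threshold holds only if students are independent, whereas the article reports ICCs up to .03, assumes .10 for its school-level power, and promises to control for school.

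The correction is minor. It concerns a secondary aim and leaves the primary mixed-model analysis and the school-level power calculation untouched.

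**What to change.** 1. Delete the wording that presents 100 df as the most complex and hence limiting case.
2. Confine the statements of ample power and of power above .80 to models with 100 df.
3. Base the SEM power claim on the smallest-df pathway model actually planned. State its df and the RMSEA values used, and use a sample size that allows for clustering by school.
4. Do not print a fixed df threshold such as 6.
5. Where the smallest model falls below .80, rest the mediation conclusion on the path estimates and their intervals, not on the fit test.

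The cost is a change of wording and one recalculation. No new data are needed, and the stated power may become less favourable for small models.

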#### Behavioral outcome analysis

We will undertake comparability of the two arms (intervention and control) will be undertaken, including school size and socio-demographic indicators (e.g., proportion of free/reduced school lunches, proportion of students from various ethnic backgrounds, aggregate reports of income). Our primary analytic strategy uses mixed-effects models with full information maximum likelihood, which uses all available data for point estimation and sandwich estimator for the standard errors.

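### With only 20 randomised schools, the named sandwich standard errors need a small-sample correction and a t reference, or a nominal 5% test runs at about 6–8%; the stated direction of the clustering error is also reversed

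*Protocol article*

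**What the plan says.** The Analysis section makes the school the unit of randomisation: "A cluster randomization design is proposed with random assignment by school to one of two arms: intervention or control". The Schools section gives the number of clusters, "for a total of 10 intervention and 10 control schools".

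Behavioral outcome analysis sets the primary strategy as mixed-effects models with full-information maximum likelihood for the estimates and a "sandwich estimator for the standard errors". No reference distribution, degrees of freedom or small-sample correction is named. Dichotomous outcome variates adds logistic regression for a clustered design and gives SAS GENMOD as an example.

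Between group analyses explains why clustering must be handled. It reports "small ICCs within schools for our outcome variables of interest (range: .00 to .03") from previous analyses and describes what follows if a positive ICC is ignored: "This can lead to large standard deviations", then larger p values and false negatives. The next sentence says the analytic strategy takes the ICC into account. The power statement begins "Assuming 20 schools, 60 students per school" and uses an ICC of .10.

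**The concern.** There are two separate points.

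**Standard errors.** A sandwich variance is built from squared residuals, and the fitted arm means have already drawn those residuals towards zero. With hundreds of clusters the shortfall is negligible. With 10 per arm it is not. In addition, the variance is estimated from 20 school-level quantities, so a normal reference distribution is too narrow. Both effects make confidence intervals too short and make it too easy to declare the programme effective. The sandwich is the named basis for inference in the primary analysis, so the question reaches the main result.

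**Direction of the clustering error.** Treatment is constant within a school. Positive correlation among students in a school therefore makes an arm mean less precise than independent sampling would suggest. An analysis that ignores this has standard errors that are too small and too many false positives. The article says the reverse. A reader who accepts its sentence would think that clustering mistakes only cost power, and would see no reason to guard against standard errors that are too small.

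**Working it through.** **Inputs.** J = 20 schools, 10 per arm (Schools); m = 60 students per school (Between group analyses); ICC .01 and .03, within the reported range of .00 to .03, and .10 as used for power. Two-sided alpha of .05 is assumed, because the article gives .05 only for the structural equation power statement.

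**The plan's own figure.** The article gives no type I error figure to reproduce. Its detectable effect of d = .27 is a different matter: (1.96 + 0.842) × √[4(ρ + (1 − ρ)/60)/20] gives 0.42 at ρ = .10 and 0.27 at ρ = .03. Nothing below depends on it.

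**1. Uncorrected sandwich, equal school sizes, arm effect only.** The estimate is a difference in means of school means. The sandwich divides each arm's sum of squared school deviations by 10 where the unbiased variance divides by 9, so its expectation is 9/10 = 18/20 = 0.90 of the true variance. With normal school means the size is exactly 2·P(t18 > c·√0.90), where c is the critical value used:
- normal reference, c = 1.960: 2·P(t18 > 1.859) = **7.9%**
- t18 reference, c = 2.101: 2·P(t18 > 1.993) = **6.2%**

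The ICC does not enter this result. Simulation at ICC .01, .03 and .10 (20,000 replicates each) gave 7.8–8.4% with the normal reference, for equal and unequal school sizes.

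The same factor applies to a comparison of change over time, because the 20 school-level change scores again split 10 and 10. A simulated two-wave contrast with a normal reference gave 7.6% at ICC .03 and 8.0% at ICC .10.

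**2. With cohort and one school-level covariate (assumed, not in the article).** Simulated size was 9.9–10.9% with a normal reference and about 8–9% with t18.

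**3. After correction, balanced case.**
- Kauermann–Carroll rescales the residuals by √(10/9), which restores the unbiased variance. With t18 the size is 5%; simulation of the unbiased variance with t18 gave 4.9–5.2%.
- Mancl–DeRouen rescales the residuals by 10/9, so its variance averages 0.90 × (10/9)² = 1.11 of the truth. The size is 2·P(t18 > 2.101 × √1.11) = 2·P(t18 > 2.215) = 4.0%, slightly conservative.
- Interval width, unbiased variance with t18 against uncorrected with z: 2.101/(1.960 × √0.90) = 1.13, so about 13% wider.

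**4. Direction of the clustering error, single-time comparison between arms.** The design effect is 1 + 59ρ, the naive standard error is 1/√(1 + 59ρ) of the true one, and the naive size is 2·Φ(−1.96/√(1 + 59ρ)).

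| ICC | Design effect | Naive SE / true SE | Naive size |
|---|---|---|---|
| .01 | 1.59 | 0.79 | 12% |
| .03 | 2.77 | 0.60 | 24% |
| .10 | 6.90 | 0.38 | 46% |

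Ignoring the ICC therefore gives smaller p values and more false positives.

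**The case against.** **The article does not say the sandwich is uncorrected or normal-based.** This is the strongest reply, and it stands as a limit. A correction or degrees-of-freedom rule may sit in an analysis plan that is not shown. A reader might infer that the trial will run at 8–10% false positives, or that intervals for every outcome will be too narrow; the text does not establish either. What remains is that the article commits to an estimator with a known bias at this number of clusters, and a better choice is cheap.

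**The upper end rests on inputs that are not in the article.** This is correct. No variation in school size is given, and the Schools section says the schools will be similar in approximate size. With mixed-model weights, coefficients of variation of .4 and .6 in school size leave the size at about 8.0%. The 10% figure comes only from the assumed extra school-level terms.

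**Maximum likelihood rather than REML is not a second bias.** This also stands. In the balanced case maximum likelihood divides the between-school sum of squares by 20 instead of 18, which is the same 10% shortfall. The two do not add up, but dropping the sandwich and keeping maximum likelihood would not remove the problem.

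**The reversed sentence is rationale only.** This stands. A reader might infer that the plan treats clustering as harmless, or take the 24% and 46% as this trial's error rates. The following sentence says the ICC is taken into account, so those figures describe an analysis the plan rejects.

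**The primary aim is change over time.** If a school's effect is perfectly stable, it cancels from a two-wave contrast, and ignoring the ICC is then mildly conservative: 2·Φ(−1.96/√(1 − ρ)) = 4.7% at ρ = .03 and 3.9% at ρ = .10. School-by-time variation would raise these values, and the article gives no figure for it. The table in the working therefore applies to single-time comparisons between arms. The sandwich result is unaffected.

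**Conclusion.** The concern holds in a conditional form and should be addressed before analysis. With 10 schools per arm, the named sandwich estimator gives a true size of about 6% (t18 reference) to 8% (normal reference) at a nominal two-sided 5%, unless a small-sample correction is applied. It could reach about 10% if cohort and a school-level covariate enter the model. The 6–8% range rests on equal school sizes, approximately normal school means and the assumed alpha; the 10% rests further on model terms that the article does not specify. With a corrected variance and t18 the size is about 5%.

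The direction of the clustering error is stated wrongly for a between-arm comparison randomised by school. This is an error of explanation and does not alter the planned analysis.

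**What to change.** In Behavioral outcome analysis, state that continuous outcomes will be analysed by REML mixed models with Kenward–Roger degrees of freedom. For the dichotomous models, where they are fitted by generalised estimating equations, state that a bias-corrected sandwich (Kauermann–Carroll or Mancl–DeRouen) will be used, with a t reference on the number of schools minus the number of school-level parameters: 20 − 2 = 18 with arm only, 17 if cohort is added. If the full analysis plan already does this, say so.

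In Between group analyses, replace the sentence on consequences with one saying that, for a comparison between arms randomised by school, ignoring a positive ICC understates standard errors and inflates false positives.

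The cost is two or three sentences and standard software options. Intervals become about 13% wider than the uncorrected normal-based ones in the balanced case, which is the honest width for 20 schools. The second change costs nothing in the analysis.
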